### Study outcomes

Primary outcomes are 1) the prevalence of different sleep disorders as a function of individuals’ mental disorders (depressive disorder, bipolar disorder, anxiety disorder, PTSD, AD(H)D, ASD, SSD or personality disorder), and 2) the effect of sleep interventions on sleep, severity of specific symptoms of mental disorders, general functioning, and quality of life. Secondary outcomes are 1) the effects of sleep interventions on objective outcome parameters, for example use of sleep/sedative medication, number of hospitalizations and length of stay and, 2) differences between genders in the prevalence of specific sleep disorders and sleep intervention effects.

First, we expect that the prevalence of most sleep disorders among individuals with mental disorders will exceed those in the general population. Second, concerning the adjusted sleep interventions, we expect that the treatment of sleep disorders, tailored to mental disorders, will improve sleep, recovery from mental disorder symptoms, and quality of life in most patients. We hypothesize that the effect of added sleep intervention(s) will be larger than the effect of TAU alone in the TAU-SI-T1 group.

### Measures/ materials

All scales used in this study will be administered in the Dutch language and have been validated for use in Dutch.

#### Sleep

The HSDQ [22] is a 32-item self-assessment questionnaire for sleep disorders, based on the International Classification of Sleep disorders (ICSD-2) [24]. Each item consists of a self-description (i.e. “I have difficulty falling asleep”) and participants are instructed to respond on a 5-point Likert scale indicating if the stated item applies to them for the past 3 months (1= “not at all”, 2 = “usually not”, 3 = “sometimes”, 4 = “usually”, 5 = “completely”). This questionnaire is validated (Cronbach’s alpha (α) = .90) [22] and screens for the following categories of sleep disorders: Chronic insomnia (α = .92), parasomnia (α = .85), CRSD (α = .84), hypersomnia (α = .78), sleep-related movement disorders (i.e. restless legs syndrome (RLS)) (α = .81), and SRBD (i.e. obstructive sleep apnea (OSA)(α = .62)) [23]. The total score of the HSDQ distinguishes individuals with a clinically diagnosed sleep disorder from individuals without sleep complaints (area under the curve, *P*(A) = .95) and the diagnostic accuracy of the HSDQ is high (kappa = .80) [22]. In the present study, the HSDQ will be used for screening purposes and to assess sleep disorder prevalences. Mean scores will be calculated and the following cut-off criteria will be used: Sleep disorder > 2.02; chronic insomnia > 3.68; parasomnia > 2.42; CRSD > 3.42; hypersomnia > 2.9; sleep-related movement disorder > 2.7; SRBD > 2.87 [22]. For the analysis of sleep treatment effect on response of the clinical sleep disorder(s), the HSDQ total and subscale scores will be used as outcome variables.

#### Quality of life

##### *Manchester Short Assessment of Quality of Life* (MANSA)

The MANSA will be used to assess quality of life. The MANSA is a 16-item self-rating scale with sufficient internal consistency (α = .74) [25]. The questionnaire addresses the following aspects: Living circumstances, work circumstances, financial circumstances, friendships, family relations, leisure time, personal safety, sexual relationships, mental health and physical health. There are 4 questions that can be answered with “yes” or “no”, the other items will be scored on a 7-points scale: “could not be worse”, “dissatisfied”, “mostly dissatisfied”, “neutral”, “mostly satisfied”, “satisfied” or “could not be better”. A total score will be calculated whereby a higher score indicates a higher quality of life.

##### *Individual Recovery Outcome Counter* (I-ROC)

In this study we will use the I-ROC, a 12-item self-rating scale designed to measure personal recovery. The I-ROC is a valid and reliable recovery outcomes measure, with a sufficient high internal consistency (α = .86) [26]. The questionnaire focusses on the following themes: Mental health, life skills, safety and comfort, physical health, exercise and activity, purpose and direction, personal network, social network, valuing myself, participation and control, self-management, and hope for future [26]. Participants will be asked to score each item on a 6-point Likert scale, ranging from 1 (= “never”) to 6 (= “all of the time”), where each rating refers to the past 3-month period. A higher total score intents to represent a greater level of personal recovery.

#### General functioning

To assess changes in general functioning, the Outcome Questionnaire (OQ-45) [27] will be employed. In this 45-item self-report questionnaire participants will be asked to answer the items based on how they have felt over the past week on a 5-point Likert scale, ranging from 0 (= “never”) to 4 (= “always”). The OQ-45 is a validated instrument with good internal consistency (α = .93) [27]. The OQ-45 was shown to be sensitive to treatment effects in heterogeneous patient samples [28]. The questionnaire originally consists of 3 different subscales: 1) Subjective Distress, 2) Interpersonal Relations and 3) Social Role. In this study we will use the Dutch version of the OQ-45, in which an extra subscale has been added and validated: Anxiety and Somatic Distress [29]. The psychometric properties of the Dutch OQ-45 are adequate and similar to the original instrument [29]. The total score and the four subscale scores of the OQ-45 will be used as outcome parameters.

#### Specific mental disorder symptoms

One (or more) of the following questionnaires, depending on the participant’s main DSM-5 diagnosis, will be used to assess specific symptomatology. Total scores will be used as outcome parameters and participants will be invited to fill out the questionnaire at all three time points.

##### Quick inventory of depressive symptomatology, self-report (QIDS-SR_16_)

The QIDS-SR_16_ [30] is a 16-item self-report scale that will be used to assess depressive symptomatology, in individuals with a depressive or bipolar disorder diagnosis. Participants are asked to answer the items by selecting one out of four statements that fitted them best in the last week. The QIDS-SR_16_ is a validated instrument with good internal consistency (α = .86) and sensitivity to symptomatic change following treatment [30].

##### Altman self-rating mania scale (ASRM)

The ASRM [31] is a 5-item self-rating questionnaire that measures mania symptoms. This questionnaire is used in individuals with a bipolar disorder diagnosis, in addition to the QIDS. In each item participants will be asked to select one out of five statements that best summarizes the way they felt in the last week. The ASRM is a validated scale, with sensitivity to change following treatment [31].

##### Spielberger state-trait anxiety inventory, Dutch-Y (STAI-DY)

The STAI is a brief self-report scale designed to measure and differentiate between anxiety as a trait and a state. In this study a Dutch version (STAI-DY) [32] will be used to assess anxiety symptoms in individuals with anxiety disorder diagnosis. Participants are asked to only fill out the state section of the STAI-DY. They will be asked to rate 20 statements on a 4-point scale ranging from “not at all” to “very much so”. The STAI-DY has been validated and the internal consistency is good (α between .91 and .95) for both individuals who are treated in outpatient and inpatient centers for mental health care [32].

##### Posttraumatic stress disorder checklist for DSM-5 (PCL-5)

The PCL-5 [33] is a 20-item self-respond measure of PTSD symptomatology, in individuals with a PTSD diagnosis. Participants are asked to describe their worst stressful experience and after this, to provide a symptom severity rating that ranges from (0=) “not at all” to (4=) “extremely”. The PCL-5 is a psychometrically sound instrument with good internal consistency (α = .94) [34] and useful for detecting clinical change over time in symptoms after treatment [35].

##### Adult ADHD self-report scale (ASRS-v1.1)

In this questionnaire participants are asked to rate a list of symptoms on a 5-point scale, ranging from (0=) “never” to (4=) “very often”, in order to assess ADHD symptoms in individuals with an ADHD diagnosis. The ASRS originally consists of 18 items. In this study we will make use of a shorter form of the ASRS (ASRS-v1.1), in order to reduce the burden to the participants. This 6-item screening version has shown to outperform the full version in sensitivity (68.7% versus 56.3%) and specificity (99.5% versus 98.3%) [36].

##### Autism spectrum quotient (AQ-50)

The AQ [37] will be used to assess autism-related symptoms in individuals with an ASD diagnosis. The AQ consists of 50 items assessing personal preferences and habits. Participants rate to what extent they agree or disagree with the listed statements on a 4-point Likert scale with answer categories: “definitely agree”, “slightly agree”, “slightly disagree”, and “definitely disagree”. The AQ is a valid and reliable instrument to assess individual differences in autistic traits and the internal consistency of the Dutch AQ is satisfactory (α = .71) [38].

##### PHAMOUS-basis psychosevragen

This short questionnaire will be used to assess symptom severity in individuals with a SSD diagnosis. Participants are asked to indicate if they have experienced the nine listed symptoms in the past 14 days by answering: 0 = “no”, 1 = “yes, probably”, or 2 = “yes”. The average item-score will be used as outcome variable. This questionnaire is currently being validated.

##### Positive and negative syndrome scale (PANSS)

In addition to the “PHAMOUS-basis psychosevragen”, in individuals with a SSD diagnosis assessments will be made on positive and negative symptoms at T0 and T2 as part of the ROM, using the Positive and Negative Syndrome Scale (PANSS) [39] interview. The PANSS is a validated 7-point, 30-item rating instrument, with each point representing increasing levels of psychopathology: 1 = “absent”, 2 = “minimal”, 3 = “mild”, 4 = “moderate”, 5 = “moderate-severe”, 6 = “severe”, and 7 = “extreme” [39].

### Sleep disorder diagnosis

The sleep diagnostic process depends on the suspected sleep disorder(s) indicated by the HSDQ. Each participant scoring positive for one or more (types of) sleep disorder(s) will be invited for a sleep diagnostic interview by trained psychologists. Participants will also be asked to complete one or more short questionnaires (5–10 min) during this interview, depending on the HSDQ-indicated sleep disorder(s). The following questionnaires will be used: the *Pittsburgh Sleep Quality Index* (PSQI) [40] for subjective quality of sleep; *Insomnia Severity Index* (ISI) [41] in participants with HSDQ-indicated Insomnia disorder; *Morningness - Eveningness Questionnaire* [42] in participants with HSDQ-indicated CRSD; *Epworth Sleepiness Scale* (ESS) [43] in participants with HSDQ-indicated SRBD and/or hypersomnia and; *International RLS study group rating scale* (IRLS) [44] in patients with HSDQ-indicated RLS. An additional file is added, and describes the sleep-oriented questionnaires in more detail (see Additional file 1). In order to evaluate the effect of sleep disorder treatment, the same questionnaires will also be filled out by the participants directly following the sleep intervention.

The diagnostic interview takes around 30–60 min. Hereafter, participants will be asked to wear an actigraph (Motionwatch 8, CamNtech) for two weeks in case of CRSD, and for one week in all other cases. This actigraph is a diagnostic instrument in the form of a wristband that registers bodily activity in order to asses objective sleep quality and sleep-wake pattern. Additionally, participants will be asked to complete a sleep diary for the same time period they wear the actigraph, in which they note their bedtimes, estimated sleep latency, total sleep duration, sleep quality, and number of awakenings. If further information is needed for diagnosis, additional diagnostic measurements will be made, such as polysomnography, Dim Light Melatonin Onset (DLMO) measurement to determine the circadian rhythm in CRSD and Multiple Sleep Latency Test (MSLT) to evaluate hypersomnia. For diagnosing sleep disorders, ICSD-3 criteria [4] will be followed. Final diagnosis will be made during a multidisciplinary consultation with a somnologist, a somno-technologist and psychologists. Complex cases will additionally be discussed with a neurologist, pulmonary-specialist, and/or psychiatrist.

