**Fig. 1 Fig1:**
[figure not shown]
Study procedure. Patients who score above the cut-off score for any type of sleep disorder on the Holland Sleep disorders Questionnaire (HSDQ+) will be invited for extensive diagnostic evaluation, followed by patient-targeted sleep treatment. Those participants will be randomly divided in one of two conditions: in TAU+SI-T0 sleep diagnosis and sleep intervention (SI) will start immediately (T0), in addition to the treatment as usual (TAU). In TAU+SI-T1 sleep diagnosis and SI will start after 6 months (T1). Questionnaires will be filled in at T0, T1 and T2 (after 12 months), measuring sleep, general functioning, specific mental disorder symptoms, and quality of life. For patients scoring below the cut-off score for a sleep disorder (HSDQ-), participation is limited to filling out the questionnaires at T0

This research project will be conducted in collaboration with a sleep centre for psychiatry. Anamnestic interviews, diagnostic assessments and sleep interventions will be provided by trained staff.

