### Statistical analyses

#### Data exploration/ missing data

Separate analyses will be performed for the different questionnaires, using SPSS (version 23) and R software. If data are not normally distributed, data transformations will be performed. A data management plan was generated using online software and can be found at DMPonline (https://dmponline.dcc.ac.uk/).

If a participant stops participation halfway the study or if a specific questionnaire is missing at a specific time point this will be dealt with as follows: if the last data point (T2) is missing, the participant will be included in the analysis for the prevalence and in any analysis focussed on de comparison between T0 and T1. For those participants that are missing a complete questionnaire at T1, but do have the T2 measurements, T1 will be treated as a missing data point and imputed using multiple imputation. If a participant is missing both the T1 and T2 data point, this participant will only be included in the prevalence analysis.

Because we make use of a delayed start for the sleep treatment in the TAU-SI-T1 group, there is a possibility that some participants in the TAU-SI-T1 control group score above the cut-off score for a sleep disorder on the HSDQ at T0, but below the cut-off score for a sleep disorder at T1. In this case, these participants will be informed about the change in their HSDQ score, and that they are no longer eligible for sleep disorder treatment, and thus excluded from the treatment part of the study. Another scenario is that a participant scores above a cut-off score of the HSDQ, but that the sleep disorder is not confirmed in the diagnostic evaluation. In this case, the participant will also be excluded from the treatment part of the study.

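### The sleep-specific questionnaires are meant to evaluate sleep treatment, but controls have no T0 value and no change over the untreated six months, so on these scales the evaluation is an uncontrolled before-after comparison

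*Protocol article*

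**What the plan says.** Under Sleep disorder diagnosis, the first administration of the sleep-specific scales belongs to the diagnostic interview: "Participants will also be asked to complete one or more short questionnaires". The PSQI covers subjective sleep quality, and the ISI, Morningness-Eveningness Questionnaire, ESS and IRLS are given according to the disorder that the HSDQ indicates. The second administration has an explicit evaluative purpose, the effect of sleep disorder treatment, and is timed as follows: "the same questionnaires will also be filled out by the participants directly following the sleep intervention". No other administration of these scales is described.

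The Fig. 1 legend fixes when the interview happens. For the early arm, "in TAU+SI-T0 sleep diagnosis and sleep intervention (SI) will start immediately (T0"). For controls, "In TAU+SI-T1 sleep diagnosis and SI will start after 6 months (T1").

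Data exploration/ missing data foresees controls who are above the HSDQ cut-off at T0 "but below the cut-off score for a sleep disorder at T1". They are told that "they are no longer eligible for sleep disorder treatment, and thus excluded from the treatment part of the study".

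The designated sleep outcome is a different instrument. The Sleep measures section states that "the HSDQ total and subscale scores will be used as outcome variables", and Effect of sleep disorder treatment compares the randomised groups over T0, T1 and T2 with linear mixed models.

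**The concern.** The trial has a randomised six-month period in which one arm receives sleep treatment plus TAU and the other receives TAU alone. The hypothesis under Study outcomes depends on that contrast: "We hypothesize that the effect of added sleep intervention(s) will be larger than the effect of TAU alone in the TAU-SI-T1 group". The sleep-specific scales are given the task of evaluating treatment, yet their schedule follows each patient's own treatment and not the randomised period. Any improvement that would have occurred under TAU alone is then part of the measured change. Such improvement is not hypothetical, because the plan itself expects some controls to drop below the HSDQ cut-off by T1 without sleep treatment.

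What is at stake is how results on these scales may be read. If before-after changes on the ISI or ESS are reported from within a randomised trial, readers may take them as randomised evidence. An analysis plan written later cannot repair this, because control values that were not collected at T0 cannot be recovered.

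**Working it through.** The plan states no figure on this point that could be reproduced. The check sets the schedule out by arm.

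**Inputs.** Administration times come from Sleep disorder diagnosis, interview timing from the Fig. 1 legend, the exclusions from Data exploration/ missing data, and the planned 236 per arm from Table 2.

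| Sleep-specific scales | About T0 | About T1 | End of sleep treatment |
|---|---|---|---|
| TAU+SI-T0 | yes, before sleep treatment | none scheduled | yes, at a patient-specific time |
| TAU+SI-T1 | none (0 of 236 planned) | yes, before sleep treatment, only if still HSDQ-positive | yes, at a patient-specific time |

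For comparison, the HSDQ is planned in both arms at T0, T1 and T2.

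**What each possible contrast estimates.** Let e be the effect of sleep treatment and u the change that would have occurred under TAU alone over the same interval.

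1. *Before-after change in the early arm:* e + u(from intake to end of treatment). Nothing is subtracted, so the error equals u.
2. *Before-after change in controls:* e + u(from about month 6 to end of treatment). The form is the same, in a later phase of TAU and in patients selected at T1.
3. *Difference between these two changes:* e cancels if it is the same in both arms. What is left is the difference between the two u terms. This does not estimate sleep treatment plus TAU against TAU alone.
4. *Early arm's end-of-treatment value against the controls' value at about T1:* this sets treated against untreated patients, but it has three defects. There is no control baseline, the times are not aligned, and controls who fell below the cut-off while untreated are missing. If these scales move with the HSDQ (an assumption), the remaining controls have worse sleep than the full control arm, which would favour the intervention.

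The HSDQ comparison has none of these scheduling gaps. Both arms are measured at the same times from T0, so the difference between arms at T1 removes u.

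**Size.** The error in contrast 1 is exactly u. The document gives no value for u on any of these scales and no expected effect on them, so no number follows.

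**The case against.** The strongest reply is that these scales are not the trial's sleep outcome. They appear under diagnosis and, apart from the PSQI, are given selectively. They are not named under Study outcomes or in the Sleep measures section. The HSDQ is the designated outcome, with favourable published properties in that section (alpha .90, area under the curve .95, kappa .80), and it is compared between randomised arms. All of this stands. A reader might infer that the trial's whole sleep evaluation is uncontrolled, or that the hypothesis under Study outcomes will be tested on before-after changes. The document supports neither reading.

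A reader might also infer that no untreated control data exist on these scales. That is too strong, because controls complete them once at about T1, before any sleep treatment. What is missing is a baseline and a change, and the single value is selected as described above.

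It is also tempting to assume an untreated change of, say, 0.2 to 0.4 SD and set it against the target effect of d = 0.4. The assumed change has no source in the document. Sample size calculations sets that d for quality of life, general functioning and disorder-specific symptoms, not for sleep, so the ratio would have no meaning here.

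Regression to the mean should not be pressed either. Selection is on the HSDQ, and the before-value comes from different instruments at a later interview, so the selecting error does not carry over directly. TAU effects and natural course are enough for the point.

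Finally, Design and the Fig. 1 legend speak generally of sleep questionnaires at three time points. The measures section ties this to the HSDQ, while the other scales have their own schedule. The general wording therefore does not fill the gap.

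The reply does not remove the stated purpose: the protocol assigns these scales a treatment-evaluation role that their schedule cannot support.

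**Conclusion.** The point holds with limited scope. On the PSQI, ISI, Morningness-Eveningness Questionnaire, ESS and IRLS, the described evaluation is a within-patient before-after comparison that cannot separate sleep treatment from TAU or natural course. By design, no control has a T0 value or a change over the untreated six months, and the early arm has no value scheduled at T1. This rests on reading the two stated administrations as the complete schedule for these scales, since the article describes no others. The randomised sleep comparison on the HSDQ is untouched. The direction and size of any bias on the sleep-specific scales cannot be derived from the document. This is a worthwhile and inexpensive improvement to supplementary evidence, not a threat to the main analysis.

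**What to change.** Give the scales indicated by the T0 HSDQ to both arms at two fixed times:

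- at T0, after consent and before randomisation or disclosure of allocation;
- at T1, before controls begin sleep diagnostics and regardless of HSDQ status at T1.

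Let the T0 HSDQ alone decide which scales a participant completes, so that the set is the same in both arms and at both times. Compare the arms at T1 and name this a supplementary sleep outcome beside the HSDQ. Keep the end-of-treatment administration as a descriptive, uncontrolled measure, and do not present it as evidence of efficacy.

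The cost is about 5-10 minutes of extra participant time per set, using the protocol's own time estimate. The existing online outcome platform can carry the questionnaires where it runs. Procedure says that routine assessments are conducted in most departments, so the others need another route. If the extra burden is judged too high, the minimum change is to state under Sleep disorder diagnosis that the evaluation on these scales is exploratory and uncontrolled.
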